### **D.3 Collect early data on the effect of the CHICA system on services provided to children diagnosed with ASD and how these affect patient outcomes. (Aim 3)**

At this time, the services that should be provided for children with ASD are not stipulated; moreover, the effect of individual services on patient outcomes is not well understood. However, there is a general sense that services should be given as early as possible, and that more services are better. We will therefore take advantage of the CHICA system to gather data on how the system affects the number of activities/involvements that children with ASD receive and how it affects patient outcomes. The data collected may provide information on how services affect outcomes and on how CHICA affects both. These data will be instrumental in further studies of both the CHICA system and autism care, in general.

#### **D.3.1 Intervention Group**

The intervention will include the enhanced version of the CHICA hardware and software, the CHICA ASD care and management module, and user support. Because the intervention is at the clinic level, all patients qualifying for the study will be automatically cared for by the CHICA ASD care and management module as part of routine care in the intervention practices. The CHICA ASD care and management module will provide the pediatrician with a number of recommendations and reminders that we expect will improve the management of patients diagnosed with an ASD. CHICA can prompt physicians to check that children with ASD are receiving the necessary services that will maximize their potential and quality of life. These can include:

- *Educational Interventions.* Specific and age-appropriate interventions could include comprehensive programs for young children inclusive of strategies and methods appropriate to ASD and evolving from applied behavior analysis, structured teaching, developmental models, speech and language therapy (e.g., conversational skills, social-relating skills), occupational therapy (e.g., fine motor and sensory integration methods)
- *Medical Management.* Like all children, those with ASD need basic health promotion and disease prevention care, such as immunizations. However, further care should be paid to the management of seizures, gastrointestinal problems, sleep disturbances, and challenging behaviors
- *Family Support.* Families play a key role in the care and management of children with ASD, and support should be given for education, emotional support, and advocacy for their children's needs

Based on the best available evidence CHICA can guide physicians through what activities and involvements should be considered for inclusion in a treatment and management program for children diagnosed with ASD. Examples of these are provided in Figure 9

- [figure not shown]
- ✔ **Speech Therapy** (focused on pragmatic and social skills)
  - ✔ **Occupational Therapy** (focused on fine motor and sensory issues)
  - ✔ **School District Autism Consultant** (if appropriate)
  - ✔ **Developmental Physician and/or Psychiatrist**
  - ✔ **First Steps and/or Special Education Services**
  - ✔ **Behavioral Therapist** (for parent education and/or intervention)
  - ✔ **Medicaid** (3 relevant waivers in the State of Indiana)
  - ✔ **Neurology** (Evaluation and treatment of concomitant seizure/neurological disorders)
  - ✔ **Genetics** (Rule out of comorbid and/or contributing diagnoses)
  - ✔ **Audiology** (Rule out hearing impairment)
  - ✔ **Gastroenterology** (Management of intestinal issues)
  - ✔ **Individualized Education Plan**
  - ✔ **Behavior Intervention Plan or Individualized Family Support Plan**

**Figure 9. Activities/Involvements Recommended for Children with ASD**

#### D.3.2 Control Group

Control clinics will also have the CHICA system in place, and therefore all patients in the control clinics will be automatically cared for by the CHICA system. However, the CHICA system within these control clinics will NOT include the ASD care and management module. Care for children diagnosed with ASD will use standard methods.

#### D.3.3 Eligible Patients

Eligible patients within each practice include children who are seen in one of the four clinics participating in this study. For evaluating the management of ASD only children ages 18 months through 5 years with newly diagnosed ASD will be eligible for the study. Additionally, at least one of the child's parents must speak English and be available to be contacted by telephone.

#### D.3.4 Patient Recruitment and Consent

The same four clinics utilized in aim 2 of the study will be utilized for aim 3 of the study. The same two clinics that served as the intervention group in aim 2 will once again serve as the intervention group for this portion of the study. These two clinics will have the ASD care and management module as part of the CHICA system. The two control clinics will have the CHICA system but will NOT have the ASD care and management module.

For this portion of the study, consent will be obtained from those patients who are newly diagnosed with ASD so that we may collect additional evaluation and assessment data beyond that which is normally documented during standard care practices. Children and their parents will be recruited and consented through the Pediatric Research Network (PResNet). PResNet is a pediatric practice based research network located at the Indiana University School of Medicine (See full description in Resources section of the proposal). PResNet was established in 2006 as an offshoot of ResNet, the very successful practice-based research network of the Indiana University Medical Group. Since 2000, ResNet has been involved in more than 40 studies supported by over \$15 million in extramural grants. In these studies, ResNet has recruited more than 7,000 patients, approximately 68% of those patients contacted (a remarkable figure, considering that two-thirds of those approached were African-American or Hispanic). In 2006, PResNet was established to facilitate pediatric specific primary care research efforts. While it does not have as long of a track record of recruiting patients as ResNet, it follows the same processes and procedures and therefore has encountered the same level of success at patient recruitment. PResNet has been involved with 8 studies in the IUMG clinics and has recruited more than 2200 patients, approximately 84% of those patients contacted. With the inclusion of the private practices, PResNet has recruited over 5000 patients, approximately 85% of those patients contacted.

Each week, the PResNet RA will be given a list of potentially eligible children who were diagnosed with ASD in one of the four study clinics during this study. Children will be identified by looking for ASD diagnostic billing codes or diagnostic codes using the RMRS. The RA will confirm the diagnosis with the physician and then contact the child's parent via telephone in order to assess eligibility, describe the study, and invite their participation. PResNet has a business associate's agreement (BAA) with the Indiana University Medical Group and is, in fact, the research arm of that organization. Therefore, the PResNet RA will introduce him/herself as calling from the child's doctor's office on behalf of the doctor. If the parent expresses interest, the PResNet RA will arrange to meet with them preferably at their next clinic visit. After the child checks into the clinic for their appointment, the RA will talk with the child and parent in a private space, usually an exam room. At that time, the RA will assess eligibility, administer the HIPAA authorization, complete the informed consent form and collect additional contact information.

#### D.3.4 Data Collection

To evaluate the effect of the CHICA system on the management of ASD patient we will collect data related to various process and outcome measures with our primary outcome of interest for aim 3 being the number of activities/involvements that a child diagnosed with an ASD is receiving.

*Process Measures.* Listed in Figure 9 are examples of activities and involvements that should be considered for inclusion in a treatment and management program for children diagnosed with ASD. We will create a checklist of these various activities and involvements that will be used to evaluate the individual components of a child's ASD management program ([name] and [name]). We will collect these data at six months and 12 months after diagnosis from reviews of the medical record and short 15 to 30 minute interviews with parents. We anticipate that those patients cared for in the two clinics with access to the CHICA ASD care and management module will demonstrate a higher number of these recommended activities/involvements.

*Outcome Measures.* We will also collect data on a variety of patient outcomes related to ASD care and management. These assessments (Table 1) will be conducted with study participants at baseline, 6 months, and 12 months after diagnosis. PResNet RAs will be trained by experts in ASD ([name] and [name]) on how to administer these measures to parents of participants in both arms of the study. These assessments will measure changes in the child's behavior, problem situations, adaptive skills, and social skills. Additionally we will measure changes in parent stress and parent satisfaction with autism management. For each of these measures, the parent will be the respondent. Table 1 provides information regarding the measures, format of those measures and respondent.

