the VABS has become the most commonly used measure of adaptive functioning in the developmental disabilities field. Children with autism consistently have VABS scores that are considerably lower than their IQ. Indeed, the gap between IQ and adaptive functioning often widens with time in children with autism. In a recent secondary analysis of the Research Units on Pediatric Psychopharmacology (RUPP) Autism Network study of risperidone, age equivalent scores were sensitive to change and easily interpretable. Therefore, the age equivalent scores on the Daily Living Skills scale of the VABS will be used as an outcome measure.

Aberrant Behavior Checklist (ABC). The ABC is a 58-item parent-report measure with five subscales: Irritability (includes agitation, aggression and self-injurious behaviors, 15 items); Social Withdrawal (16 items); Stereotypies (7 items); Hyperactivity (16 items); and Inappropriate Speech (4 items). The ABC is commonly used in clinical trials in children with autism and is currently being used in the RUPP and the Studies to Advance Autism Research and Treatment (STAART) studies.

Parenting Stress Index(PSI). The PSI (short form) is a 36-item parent-completed questionnaire for families of children 12 years of age and younger. It has been empirically validated. The PSI has three scales: Parental Distress, Difficult Child Characteristics, and Dysfunctional Parent-Child Interaction. The PSI Short Form is currently used by investigators in the Autism RUPP–PI group.

Parent Satisfaction with Autism Management. We will create a survey to measure parent satisfaction with how their provider handled the management of their child's ASD ([name] and [name]). This survey will be administered at baseline and at 12 months to parents in both the intervention and control groups.

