#### D.3.4 Incentives

For the clinic practices in both study arms, CHICA will be provided free. Other incentives for control practices to participate in the study will include the provision of the “Autism and Pervasive Developmental Disorders Tool Kit” developed by the HANDS in Autism Project Team at the Christian Sarkine Autism Treatment Center located at Riley Hospital for Children in Indianapolis, Indiana. For children and parents in both study arms, a \$50 cash incentive will be provided after the completion of each assessment. Assessments will be conducted at 3 month intervals – baseline, 3 months, 6 months, 9 months, and 12 months. Therefore, the total incentive available to a study participant is \$250.

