Aim 3 involves the collection of pilot data and hence we may not have adequate power to detect a difference between the intervention and control groups. We will collect data on the primary outcome, the number of activities/involvements (listed in Figure 9) that a child diagnosed with an ASD is receiving and on secondary multiple patient improvement outcomes at baseline, 6 and 12 months. We will model the longitudinal data on primary outcome measured at baseline, 6 and 12 months and the change in secondary outcomes. For example, change in problem behaviors, parent stress and satisfaction at 6 and 12 months from baseline. The nature of our data is complex, a three-level data structure. The three levels are occasion of measurements, patients and clinics. Patients (level 2) are nested within clinic (level 3) and repeated measurements (level 1) are nested within patient. The model for observation  $Y_{ijk}$ , that is, observation for the  $k^{\text{th}}$  patient at time  $j$  and  $i^{\text{th}}$  clinic, is given by

$$Y_{ijk} = \alpha_{0i} + \delta_{0k} + \mathbf{X}'\boldsymbol{\beta} + \varepsilon_{ijk}$$

where the independent components

$$\alpha_{0i} \text{ distributed as } N(0, \sigma_{(3)}^2) \quad \delta_{0k} \text{ distributed as } N(0, \sigma_{(2)}^2) \text{ and} \\ \varepsilon_{ijk} \text{ distributed as } N(0, \sigma^2)$$

The random component  $\alpha_{0i}$  correlates observations within the same clinic and the random component  $\delta_{0k}$  correlates repeated observations from the same patient. The vector  $\mathbf{X}$  represents fixed covariates and  $\boldsymbol{\beta}$  represents the corresponding coefficients. We will use proc mixed available in SAS to fit this model. The fixed covariates will include treatment group, time, gender, race, age, baseline value of the response variable and other potential clinical outcomes. Baseline value of the primary outcome will not be a covariate in modeling primary outcome since the response vector ( $Y_{ijk}$ ) will include the baseline outcome. We will first test for the interaction effect between time and treatment group. If there is no interaction effect, we will evaluate the overall treatment difference. Otherwise, treatment difference will be assessed at each time point. If there is a significant difference, we will report the 95% confidence interval after adjusting for all confounding factors.

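### The Aim 3 measurement schedule contradicts itself on the baseline value of the primary outcome, the number of assessments, and the 6-month satisfaction survey

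*Protocol*

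**What the plan says.** D.3.4 Data Collection names the "primary outcome of interest for aim 3 being the number of activities/involvements that a child diagnosed with an ASD is receiving". The checklist that yields this count is a process measure, and its timing is given as: "We will collect these data at six months and 12 months after diagnosis from reviews of the medical record". Short parent interviews of 15 to 30 minutes are the second source. The next paragraph turns to the patient outcome measures: "These assessments (Table 1) will be conducted with study participants at baseline, 6 months, and 12 months after diagnosis". Table 1 lists five such measures, and parent satisfaction is one of them. The later description of that survey says: "This survey will be administered at baseline and at 12 months to parents in both the intervention and control groups".

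D.3.4 Incentives gives another calendar: "Assessments will be conducted at 3 month intervals – baseline, 3 months, 6 months, 9 months, and 12 months". It pays $50 for each completed assessment and states a total of $250.

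D.5.2 says that the primary and secondary Aim 3 outcomes will be collected at baseline, 6 and 12 months, and continues: "We will model the longitudinal data on primary outcome measured at baseline, 6 and 12 months and the change in secondary outcomes". Its example of the secondary analyses is "change in problem behaviors, parent stress and satisfaction at 6 and 12 months from baseline". It excludes the baseline primary outcome from the covariates because that value is already part of the response. The time-by-treatment interaction is tested first, and the result decides whether an overall difference or a difference at each time is assessed.

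**The concern.** The section that tells research assistants what to collect, from which source and when does not list a measurement that the analysis section relies on. A parent interview missed at baseline cannot be fully replaced later. Record review may recover part of the count, but recall at 6 months is a different measurement.

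The baseline matters more here than in an individually randomized trial. There are two clinics per arm, and section D itself concedes that unknown characteristics related to outcome may be unevenly spread over the four clinics. Several Figure 9 items, such as speech therapy, First Steps and audiology, could be in place before an ASD diagnosis, so a starting count of zero cannot be assumed. Aim 3 is meant to supply preliminary data for a larger study, and a follow-up count with no starting value serves that purpose poorly.

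The other two conflicts leave the number of contacts and payments per family unsettled, and they plan an analysis of satisfaction at a time when its own description does not administer it.

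**Working it through.** **Times by measure, as each section gives them (months)**

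| Item | D.3.4 Data Collection | D.3.4 Incentives | D.5.2 |
|---|---|---|---|
| Activities/involvements (primary) | 6, 12 | not itemized | 0, 6, 12 |
| Table 1 measures in general | 0, 6, 12 | not itemized | 0, 6, 12 |
| Parent satisfaction | 0, 6, 12 as a Table 1 measure; 0, 12 in its own description | not itemized | change at 6 and 12 from 0 |
| Assessments overall | 0, 6, 12 | 0, 3, 6, 9, 12 | 0, 6, 12 |

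**1. Primary outcome.** The time in D.5.2 that is absent from the checklist schedule is month 0. Baseline is named in the very next paragraph for the other measures, so its absence for the checklist does not read as loose wording.

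To see what this does to the planned test sequence, write b for a true difference between arms at baseline and Δ for a treatment effect that is equal at 6 and 12 months.

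- With three times, the between-arm differences are b, b + Δ, b + Δ. The interaction test detects Δ as a departure from the baseline difference, and b can be estimated.
- With two times, the differences are b + Δ, b + Δ. There is no interaction, so D.5.2 moves to the overall difference. That difference estimates b + Δ, and the two parts cannot be separated.

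The model can therefore still be fitted on two occasions, but the interaction test then asks whether the arms diverge between 6 and 12 months. That is a different question from change since baseline.

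**2. Number of assessments.** First the protocol's own figure: 5 × $50 = $250, which reproduces. Under the schedule in D.3.4 Data Collection and D.5.2: 3 × $50 = $150. The gap is two assessments and $250 − $150 = $100 per family. Because the total agrees with the five listed times, the five-point calendar is not a typing slip. Months 3 and 9 appear for Aim 3 only in the Incentives section. No measure is assigned to them and no analysis uses them.

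**3. Satisfaction.** The survey's own description gives months 0 and 12. Its place in Table 1 gives 0, 6 and 12. D.5.2 needs month 6. If the survey's own description is followed, the 6-month change has no data.

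**The case against.** The strongest reply is that D.5.2 states collection as well as modelling at baseline, so the baseline count is planned. This stands to the extent that the baseline is not absent from the protocol. What remains is a conflict between two collection schedules, and the one without a baseline is the operational one. A later analysis plan could not settle this, because it cannot create data that were not collected.

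Three stronger readings are tempting, and the protocol does not support them.

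- A reader might infer that the baseline will be missing for every child. That follows only if staff apply D.3.4 Data Collection literally. D.5.2 says otherwise, and record review might recover some of the information.
- A reader might infer that the D.5.2 model could not be run. A random-intercept model can be fitted with two occasions per child. The meaning of its tests changes, and adjustment for age, gender and race remains available.
- A reader might infer a definite loss of power. That would compare with an analysis using baseline as a covariate, which D.5.2 rules out. Take 20 children per group, unit variance, an assumed equal correlation ρ between occasions, and clinics ignored. The variance of the between-arm contrast is (2/20) × (1 + ρ)/2 for the mean of the two follow-ups, and (2/20) × [(1 + ρ)/2 + 1 − 2ρ] for that mean minus baseline. At ρ = 0.5 both equal 0.075. At ρ = 0.3 they are 0.065 and 0.105; at ρ = 0.7 they are 0.085 and 0.045. The protocol gives no ρ, so even the direction is open. D.4 also sizes Aim 3 on estimation, and D.5.2 accepts that power may be inadequate.

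**Conclusion.** The concern holds as three internal contradictions in the Aim 3 schedule, and they should be reconciled before enrolment.

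- The checklist schedule supplies two of the three times that D.5.2 plans for the primary outcome. If it is followed, change from baseline is lost, and an initial difference between arms of two clinics each can be neither seen nor accounted for. This consequence is conditional on which section staff follow.
- The number of assessments is three or five, which means $150 or $250 per family. This is plain arithmetic on the protocol's own $50 and needs no assumption.
- The 6-month satisfaction change is planned in D.5.2 but not provided for in the survey's own description.

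The first is the most serious, because a missed baseline interview cannot be fully made good. None of the three affects the Aim 3 size of 20 per group, which does not depend on the number of measurement times.

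**What to change.** 1. In D.3.4 Data Collection, add the Figure 9 checklist to the baseline assessment already scheduled there for the Table 1 measures, so that the primary outcome is collected at baseline, 6 and 12 months as D.5.2 requires.
2. Replace the separate timing statements with one table of measures by time point, and have D.3.4 Data Collection, D.3.4 Incentives and D.5.2 all refer to it. If months 3 and 9 are kept, the table should show what is collected then and D.5.2 should say how it is used. Otherwise they should be removed.
3. Set the number of payments and the stated total to match that table.
4. Either limit the satisfaction analysis to the change at 12 months, or add a 6-month survey to its description.

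The cost is one extra checklist of 15 to 30 minutes at a contact that is already planned, plus corrected schedule and incentive text. Adding the 6-month survey would put one more questionnaire into an existing assessment; limiting the analysis to 12 months would add no burden.

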**Table 1. Patient Outcome Assessment Plan – Construct and Format**

| Measure                                    | Construct                  | Format                      | Respondent |
|--------------------------------------------|----------------------------|-----------------------------|------------|
| Home Situations Questionnaire              | Non-compliance Behavior    | Questionnaire               | Parent     |
| Vineland Adaptive Behavior Scales II       | Personal and Social Skills | Interview/
Questionnaire | Parent     |
| Aberrant Behavior Checklist                | Problem Behaviors          | Questionnaire               | Parent     |
| Parenting Stress Index                     | Parent Stress              | Questionnaire               | Parent     |
| Parent Satisfaction with Autism Management | Satisfaction               | Questionnaire               | Parent     |

Home Situations Questionnaire-Revised (HSQ-R). The original HSQ instrument developed by Barkley measures the presence of child behavior problems across 16 home situations. We will be using a version of this measure that has been adapted for use in children with Autism. This version asks parent to note whether the child has difficulties following rules or expectations in 25 different everyday situations. Questions answered by the parent affirmatively are then rated on a 1 through 9 Likert scale with higher scores indicating more severe noncompliance. Thus the scale yields two scores: a count of "yes" responses (0 to 25) and a severity score (total of 1 through 9 for all items with a "yes" response, for a range of 0 to 225). This total score is usually expressed as the per item mean (total ÷ 25).

Vineland Adaptive Behavior Scales II (VABS). The VABS assess adaptive functioning across several domains: Socialization, Communication, Daily Living Skills, Motor Skills, and an optional maladaptive behavior index. The VABS relies on the parent or primary caretaker to describe what the child actually does in the course of daily living. The scales have been standardized (mean of 100 + 15). Since its reintroduction in 1984,

the VABS has become the most commonly used measure of adaptive functioning in the developmental disabilities field. Children with autism consistently have VABS scores that are considerably lower than their IQ. Indeed, the gap between IQ and adaptive functioning often widens with time in children with autism. In a recent secondary analysis of the Research Units on Pediatric Psychopharmacology (RUPP) Autism Network study of risperidone, age equivalent scores were sensitive to change and easily interpretable. Therefore, the age equivalent scores on the Daily Living Skills scale of the VABS will be used as an outcome measure.

Aberrant Behavior Checklist (ABC). The ABC is a 58-item parent-report measure with five subscales: Irritability (includes agitation, aggression and self-injurious behaviors, 15 items); Social Withdrawal (16 items); Stereotypies (7 items); Hyperactivity (16 items); and Inappropriate Speech (4 items). The ABC is commonly used in clinical trials in children with autism and is currently being used in the RUPP and the Studies to Advance Autism Research and Treatment (STAART) studies.

Parenting Stress Index(PSI). The PSI (short form) is a 36-item parent-completed questionnaire for families of children 12 years of age and younger. It has been empirically validated. The PSI has three scales: Parental Distress, Difficult Child Characteristics, and Dysfunctional Parent-Child Interaction. The PSI Short Form is currently used by investigators in the Autism RUPP–PI group.

Parent Satisfaction with Autism Management. We will create a survey to measure parent satisfaction with how their provider handled the management of their child's ASD ([name] and [name]). This survey will be administered at baseline and at 12 months to parents in both the intervention and control groups.

